## Abstract

**Introduction:**

Obstetric hemorrhage is one of the leading causes of maternal mortality and morbidity worldwide. One of the major risk factors of obstetric hemorrhage include placenta previa and placenta accreta spectrum (PAS) disorders. The frequency of PAS disorders is increasing worldwide and is accompanied by massive intraoperative bleeding with hemorrhagic shock and increasing rates of cesarean hysterectomy. To decrease the risks of bleeding, various approaches to endovascular balloon occlusion have been tested during the past decade.

**Objectives:**

This study aimed to evaluate the effectiveness of resuscitative endovascular balloon occlusion of the aorta (REBOA) in reducing blood loss and preserving the reproductive organs during cesarean section. Study design: This will be a prospective randomized controlled trial involving 144 patients in a tertiary care obstetric center in Kazakhstan. The study population will consist of pregnant women who will be admitted for cesarean section due to placenta previa complicated by PAS disorders. The study subjects will be randomly divided into intervention and control groups.

**Results:**

The results will be analyzed through the measurement of primary (blood loss during cesarean section) and secondary outcomes [occurrence of hysterectomy during cesarean section, blood transfusion volume, duration of surgery, balloon application time, stay in intensive care unit (ICU), neonatal outcomes, complications, and total days of postsurgical hospital stay].

**Conclusion:**

The use of REBOA is expected to minimize intraoperative blood loss during cesarean section, decrease the need for transfusion of blood components, reduce the time of surgical intervention, decrease the rate of maternal complications, and reduce the rate of cesarean hysterectomy.

## Introduction

1

Obstetric hemorrhage is a global burden due to its serious impact on maternal morbidity and mortality through mechanisms such as tissue hypoperfusion, disseminated intravascular coagulation (DIC), intensive care unit admission, and multiple organ/system failure (1). One of the major risk factors for obstetric hemorrhage is placenta previa and morbidly adherent placenta (2–5). Moreover, the incidence of placenta previa and abnormally invasive placenta has been growing during recent decades due to increased rates of cesarean delivery worldwide (3, 6).

Several terms are used in the literature to define abnormally invasive placenta, including abnormally adherent placenta, invasive placenta, and placenta accreta spectrum disorders (2, 3). This study will use the placenta accreta spectrum (PAS) disorders classification proposed by FIGO (2, 7). The classification of placental invasion comprises three grades: FIGO 1 – placenta accreta, FIGO 2 – placenta increta, and FIGO 3 – placenta percreta (2, 7). There is a high risk of massive intraoperative hemorrhage during cesarean section in case of PAS disorders leading to cesarean hysterectomy in most of the cases (3). Therefore, the main goal in the management of pathologically adherent placenta is to reduce intraoperative bleeding and perform organ-sparing surgery.

In recent decades, various types of minimally invasive endovascular interventions have been studied to reduce intraoperative blood loss while preserving fertility in women with PAS disorders (8–13). These interventions include uterine artery embolization (UAE) and placement of balloon catheters in the internal iliac arteries and in the aorta (9, 10, 14).

Resuscitative endovascular balloon occlusion of aorta (REBOA) is gaining popularity for abdominal bleeding emergencies and has also been used in obstetric practice since 1995 (15). REBOA is a minimally invasive procedure in which a balloon catheter is inserted into the infrarenal part of the aorta (Zone III; proximal and distal) to control bleeding. In most of the previously reported studies, REBOA is found to be an effective method for reducing intraoperative blood loss and blood transfusion volume at cesarean section in cases of PAS (16–20). These studies concluded that the use of REBOA is associated with a decrease in intraoperative blood loss, a reduction in the need for transfusion of donor blood components, and surgical time. It is also favorable for the conservation of reproductive organ(s) and earlier transfer to the postpartum department/discharge from the hospital.

The advantage of REBOA compared to other endovascular procedures is that the procedure can be performed in a standard operating room, eliminating the need for multiple inconvenient transfers of patients between the interventional radiology department and the operating room or the use of hybrid operating rooms, thereby optimizing resources. Balloon placement is confirmed using an ultrasound device, reducing the risk of potential radiation exposure to the patient, fetus, and personnel (21, 22). Access to the vessel with REBOA is made through a single femoral access compared to the bilateral access required for the occlusion of the internal iliac and uterine arteries, which significantly reduces operating time.

The Republic of Kazakhstan is a middle-income Central Asian country with a population of 20 million with approximately 400,000 annual deliveries (23). Kazakhstan has a growing birth rate over the past decade (24), which increases the demand for high-quality maternity care. Therefore, the Kazakhstani government prioritized maternity healthcare and childcare, increasing the budget to support the healthcare system (23). Currently, the management of PAS cases is guided by the Kazakhstani national protocol on “Pathology of the Placenta” (25). According to this document, cesarean section is recommended at 36–37 weeks of gestation for cases of PAS disorders (25). In the event of intraoperative massive bleeding, the guideline suggests the administration of uterotonic drugs, application of additional hemostatic sutures, and ligation of the arteries supplying the uterus. In cases of PAS, the guideline suggests the application of UAE to minimize surgical bleeding (25). However, if the above methods are ineffective and bleeding continues, further management includes a hysterectomy. Rates of cesarean hysterectomy in Kazakhstan are comparable with other middle-income countries, with cesarean hysterectomy due to placental pathology (placental abruption, placenta previa, and PAS) reported as the second most common indication (26). The national guideline on placental pathologies management does not regulate the use of endovascular interventions in the management of PAS disorders.

Considering that no experience in the use of endovascular interventions for PAS disorders management exists in the Kazakhstani obstetrics care setting, this project will evaluate the effectiveness of REBOA in reducing blood loss and preserving the reproductive organ during cesarean section. In addition to assessing the effectiveness of endovascular treatment, this study will identify the risk factors for thromboembolic complications associated with massive bleeding, which is defined as blood loss of more than 1,500 mL. Identification and stratification of risk groups for thromboembolic complications will allow the selection of patients for minimally invasive interventions in obstetric practice in the future.

The hypothesis is that REBOA will minimize intraoperative blood loss during cesarean section, decrease the need for transfusion of blood components, reduce the rate of hysterectomy need, and decrease the time of surgical intervention and the length of patient stay in the hospital in patients with PAS disorders.

## Materials and methods

2

### Study design and study environment

2.1

This will be a prospective, randomized controlled trial (RCT) that will investigate the superiority of REBOA in combination with cesarean section compared to the traditional cesarean section for pregnant women with PAS disorders. The study was registered in the Clinical.Trials.gov database (registration ID NCT06721182) and will take place in the National Research Center for Mother and Childcare (NRCMC), University Medical Center (UMC), Astana, Kazakhstan. The NRCMC is a tertiary care leading specialized institution in the field of obstetrics and gynecology in Kazakhstan. The hospital has sufficient experience in the field of scientific research and a powerful technical and personnel base.

### Study subjects

2.2

The study population will consist of pregnant women who will be admitted to the NRCMC of UMC for cesarean section due to placenta previa complicated by PAS disorders. The study subjects will be divided into cases and controls. The following inclusion criteria will be applied for the study: (1) singleton pregnancy at 34 weeks of gestation or more, (2) age 18 to 45 years, (3) confirmed diagnosis of placenta accreta spectrum, (4) indication for elective cesarean section, and (5) consent for aortic balloon occlusion during cesarean section.

The following exclusion criteria will be followed for both, case and control groups: (1) pregnant patients at the gestational age < 34 weeks of gestation, (2) multiple pregnancies, (3) need for emergency cesarean section, (4) blood coagulation disorders (known coagulopathy, women with abnormal baseline activated partial thromboplastin time (aPTT), prothrombin time (PT), and international normalization ratio (INR) before surgery). In addition, patients on antiplatelet and anticoagulant drugs with a known history of thrombotic events will also be excluded.

### Recruitment process

2.3

The study participant recruitment will be performed from December 2024 to December 2025. Subjects who meet the eligibility criteria will be randomly assigned to either the intervention/case group (cesarean section + REBOA) or to the traditional treatment/control group (cesarean section). To ensure the control group patients’ safety, intraoperative bleeding will be managed according to the national guidelines for the pathology of the placenta (25) and postpartum bleeding management.

A simple randomization method will be applied (Figure 1). Randomization will be based on a “single sequence of random assignments known as simple randomization” (27). This technique maintains complete randomness of the assignment of a person to a particular group. The randomization procedure includes using a shuffled deck of cards (odd - intervention group, even – control group) (27). The randomization will be performed after patient recruitment, once the study aims and expected outcomes are explained to the patient and informed consent is obtained, by the responsible project team member.

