To calculate the required sample size for this outcome, probabilities of hysterectomy were derived from pooled OR (
${\mathrm{OR}}_{\mathrm{pooled}}$
 = 0.31) of meta-analysis using the following formula

$$p_{2}=\frac{p_{1}\cdot {\mathrm{OR}}_{\mathrm{pooled}}}{1-p_{1}+\left(p_{1}\cdot {\mathrm{OR}}_{\mathrm{pooled}}\right)}$$

Subsequently, the sample size was estimated based on calculated probabilities as follows:

$$\begin{array}{l} n=\frac{{\left(Z_{\alpha /2}+Z_{\beta }\right)}^{2}\times \left[p_{1}\left(1-p_{1}\right)+p_{2}\left(1-p_{2}\right)\right]}{{\left(p_{1}-p_{2}\right)}^{2}}\\ \approx 72\;\mathrm{patients}\;\mathrm{per}\;\mathrm{group} \end{array}$$

Using a sample size greater than the largest estimated requirement (n ≈ 72 per group) among major outcomes will ensure sufficient power for evaluating the impact of REBOA in minimizing blood loss during cesarean sections in patients with placenta accreta spectrum disorders, adequately accounting for the detection of previously reported effect sizes with a significance level (*α*) of 0.05 and a statistical power (1−*β*) of 80%. Thus, the calculated sample size was 72 patients per group (overall 144 patients).

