#### Cesarean section

2.6.2

Surgery will be performed according to the standard procedure following the national guideline on “Cesarean section” used in the NRCMC (37).

In order to avoid operator variability and differences in surgical techniques, the same persons (team of researchers) will be involved in surgical procedures for both groups (cases and controls).

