Future clinical and research implications. The measurable outcome of endovascular management includes the assessment of maternal intra- and postoperative complications. Major complications associated with endovascular balloon occlusion include distal ischemia, reperfusion syndrome, thrombosis, and lower extremity embolization will be analyzed and discussed in comparison with the results from previous studies. The outcomes of this research will facilitate improvements in the local guidelines on the management of placenta previa and PAS disorders. Moreover, the study results may contribute to the development of new guidelines that should prioritize the practical realities faced by developing countries, including limited access to advanced imaging, specialized surgical teams, and blood transfusion resources.

Study strengths and limitations. This will be the first study in Kazakhstani obstetric practice to investigate the efficacy of endovascular balloon occlusion for the management of pregnancy complicated by PAS disorders. The prospective randomized controlled study design will be the major strength of the study, as it will help define the difference between the two approaches (cesarean section vs. cesarean section and REBOA). A limitation of the study, however, will be the small sample size. However, due to the low prevalence of PAS disorders, the complexity of the study, and budget limitations, this sample size has been determined as appropriate based on the sample size calculation. Another limitation will be the lack of blinding for outcome assessors. However, the nature of the investigation and management procedures does not allow for blinding (45). Therefore, this study is planned as an open-label, where patients, clinicians, and care providers are aware of management (cesarean section + REBOA vs. cesarean section) allocations.

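### Allocation is by a hand-drawn card from an undefined deck, with no described concealment, independent allocator or log, in an open-label trial

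*Protocol article*

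**What the plan says.** Section 2.3 (Recruitment process) of the protocol article states the type of randomization, the device, the timing and the allocator:

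- Type: "A simple randomization method will be applied". The section adds that assignment to a group stays completely random.
- Device: "The randomization procedure includes using a shuffled deck of cards (odd - intervention group, even – control group").
- Timing: "The randomization will be performed after patient recruitment", once the study has been explained and consent obtained.
- Allocator: "by the responsible project team member". Whether this person is separate from recruitment or surgery is not stated.

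Three other places bear on the point. Section 2.4 concludes that "the calculated sample size was 72 patients per group (overall 144 patients"). Section 2.6.2 says that "the same persons (team of researchers) will be involved in surgical procedures for both groups". The limitations in the Discussion list unblinded outcome assessors and say that "this study is planned as an open-label, where patients, clinicians, and care providers are aware of management".

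**The concern.** Blinding is absent, so the randomized comparison depends heavily on nobody being able to influence which woman enters which arm. The article calls the randomized design its major strength, and that strength rests on this step.

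A card drawn by hand by a team member protects it poorly. The draw leaves nothing to check afterwards unless a record is kept, and none is described. An unwelcome card can be put back and another drawn. The person drawing may know how severe the case looks: confirmed PAS is an inclusion criterion (section 2.2), and Table 1 places ultrasound and MRI before surgery. A few overridden draws that steer severe cases to one arm would bias blood loss and hysterectomy in a direction the analysis could neither detect nor correct.

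The procedure is also not fully defined. Without the composition of the deck and the replacement rule, the allocation probability is unknown, and the claim of simple randomization cannot be checked.

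**Working it through.** No stated figure underlies the allocation method, so there is none to reproduce. The check takes the two ways the deck could be used and compares each with what the article claims. They are alternatives and cannot both apply.

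**Inputs.** N = 144, 72 per group (section 2.4). Simple randomization, odd/even cards (section 2.3). Assumption: equal numbers of odd and even cards. Deck size is not given, so 52 and 144 cards are shown as a range.

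**Case A: cards are not replaced.** Each draw changes the odds of the next, so assignments are not independent and this is not simple randomization. Take n odd and n even cards, and a person who always guesses the arm with more cards left.

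- Expected correct guesses = n + 4^n / (2·C(2n, n)) − 1/2.
- 52 cards (n = 26): 30.04 of 52 = 57.8%.
- 144 cards (n = 72): 79.03 of 144 = 54.9%.
- Expected number of final cards known with certainty = 2n/(n + 1): 52/27 = 1.93 and 144/73 = 1.97, so about two per deck.

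Simulation gave 57.7% and 54.9%, with 1.95 and 1.93 certain cards. Independent draws would give 50% and none.

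**Case B: cards are replaced and the deck reshuffled.** Draws are independent, as claimed, but there is no order fixed in advance against which an allocation could be audited, and group sizes are random. With X ~ Binomial(144, 0.5):

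- Standard deviation of one arm = √144 / 2 = 6.
- P(X = 72) = C(144, 72) / 2^144 = 0.066.
- 2.5th and 97.5th percentiles: 60 and 84.

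**Does Case B matter for power?** The control hysterectomy rate p1 is not given. The article's formula returns 72 at p1 = 0.307, with p2 = 0.121 from the odds ratio of 0.31; this p1 is an assumption (p1 = 0.879 also returns 72). At 0.307 the pooled two-proportion test has power 78.4% at 72:72. With 60 in one arm and 84 in the other it is 78.3% or 76.3%, depending on which arm is smaller. The unpooled test gives 80.0% at 72:72 and 76.6% or 81.1% at the same splits. Even at the edge of the 95% range the change is at most about 3 points, and it can go either way.

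**Redraws.** No calculation bounds the effect of repeated or overridden draws, because nothing described would reveal them.

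**The case against.** The strongest reply is that much of this rests on silence. A journal article condenses the full protocol; envelopes, a witness or a log may be described there, and Figure 1 is not shown. The draw comes after consent, and an honest draw from a well-shuffled deck is not known beforehand. This stands against one tempting reading, that allocation is unconcealed and cannot be audited: the article does not say so. It does not answer the point, because the article itself chooses the device, and a hand draw by a team member is a weak choice whatever is left to another document.

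Other readings go further than the documents allow:

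- **One group recruits, draws and operates.** Section 2.3 names a project team member and section 2.6.2 a team of researchers. That these are the same individuals is an inference.
- **The deck is not 1:1.** That needs court cards counted as 11 to 13, and the article does not say which cards are used.
- **Unequal arms weaken the trial.** They barely change power, and unequal numbers arising by chance do not bias the comparison.
- **Ignoring PAS grade is an error.** Unstratified randomization is valid, and section 2.9 plans models adjusted for confounders, though it does not name PAS grade. If 30% of women were severe (assumed), a chance difference above 10 percentage points would occur in 19.2% of trials (4.7% to 22.5% for shares of 10% to 50%). Nor does the article say that a grade is recorded before surgery for every woman: section 2.5 uses ultrasound to confirm the diagnosis, MRI for degree particularly in selected situations, and histology afterwards.
- **Concealment would cure unblinded assessment.** Hysterectomy decisions and blood-loss readings come after allocation, and concealment protects neither.

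Predictability is also modest. Fixed blocks of four would be easier to guess (n = 2 in the formula above: 2.83 of 4, or 71%). The main weakness is therefore the untraceable redraw.

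**Conclusion.** The concern holds for the allocation mechanism. Section 2.3 specifies a hand-drawn card, leaves the deck and the replacement rule undefined, and describes no concealment, independent allocator or log, in a trial where nobody is blinded. A draw can be repeated or overridden without trace, and the resulting bias cannot be sized or excluded.

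The measurable consequences are smaller. Without replacement, the claim of simple randomization is wrong and 55% to 58% of assignments can be guessed, assuming a balanced deck of 144 or 52 cards. With replacement, 72 per group has a 6.6% chance and one arm ranges from 60 to 84, with negligible effect on power.

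The documents do not show that allocation was in fact unconcealed or manipulated, and the lack of stratification by PAS grade is not an error.

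**What to change.** Replace the cards with a computer-generated 1:1 list in permuted blocks of randomly varying size. Someone already on the project, but not involved in recruitment or surgery, should prepare and hold it and should not disclose the block sizes. Conceal the list in sequentially numbered, opaque, sealed envelopes or a web module, opened only after eligibility and consent are recorded. Log every allocation with date and time.

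The planned recruitment window is December 2024 to December 2025. If recruitment has begun, switch for all remaining patients and report the date. For women already allocated, disclose the deck, the replacement rule and any record of draws.

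Optional: record the preoperative imaging assessment of PAS severity before allocation, add it to Table 2, and adjust for it or stratify by it.

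The cost is a short amendment and set-up time. The sample size does not change. The optional step requires imaging severity to be recorded before each allocation.

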**Figure 1 fig1:**
[figure not shown]
Schematic diagram of the study.

### Sample size calculation

2.4

To estimate the required sample size, effect sizes for three major outcomes (mean intraoperative blood loss, blood transfusion volume, and hysterectomy rates) were derived from previous studies examining the impact of REBOA on reducing blood loss during cesarean sections in patients with placenta accreta spectrum disorders. Due to substantial heterogeneity in the effect sizes across studies (*I^2^* for mean blood loss difference = 94.89% and *I^2^* for mean transfusion volume = 86.95%), random-effects meta-analyses were conducted on individual study-level blood loss and transfusion volumes extracted from two previously published meta-analyses (28, 29). For the hysterectomy outcome, a fixed-effect meta-analysis was applied due to lower heterogeneity (Q = 19.90, *I^2^* = 29.64%).

The meta-analysis of mean blood loss differences between REBOA and control groups, based on previous studies (28, 29), revealed a random-effects pooled estimate of −1331.46 mL (95% CI: −1643.21 to −1019.71) and a pronounced effect size (Cohen’s *d* = − 2.06). Using the pooled mean difference (
$\Delta_{\mathrm{pooled}}$
) and variance adjusted for between-study heterogeneity (
$SE^{2}+\tau^{2}$
), the required sample size was calculated as follows:

$$\begin{array}{l} n=\frac{2\times {\left(Z_{\alpha /2}+Z_{\beta }\right)}^{2}\times \left(SE^{2}+\tau^{2}\right)}{\Delta_{\mathrm{pooled}}^{2}}\\ =\frac{2\times {\left(1.96+0.84\right)}^{2}\times \left(159.06^{2}+292106.16^{2}\right)}{-1331.46^{2}}\\ =2.81\approx 3\;\mathrm{patients}\;\mathrm{per}\;\mathrm{group} \end{array}$$

Similarly, a meta-analysis of blood transfusion volume differences, based on 13 studies, yielded a pooled estimate of −975.10 mL (95% CI: −1224.25 to −725.95) with a similar effect size (Cohen’s *d* = − 2.08), resulting in a required sample size estimate of 2.99 (≈ 3 patients per group). These small sample size estimates reflect the large effect sizes observed, where the pooled mean differences are substantial relative to the pooled standard deviation, yielding a high signal-to-noise ratio. This robustness persists even after accounting for high heterogeneity in continuous outcomes.

For hysterectomy rates, fixed-effect meta-analysis across 15 studies revealed a pooled odds ratio (OR) of 0.31 (95% CI: 0.21 to 0.46) with a significant overall effect (Z = −5.84, *p* < 0.001).

To calculate the required sample size for this outcome, probabilities of hysterectomy were derived from pooled OR (
${\mathrm{OR}}_{\mathrm{pooled}}$
 = 0.31) of meta-analysis using the following formula

$$p_{2}=\frac{p_{1}\cdot {\mathrm{OR}}_{\mathrm{pooled}}}{1-p_{1}+\left(p_{1}\cdot {\mathrm{OR}}_{\mathrm{pooled}}\right)}$$

Subsequently, the sample size was estimated based on calculated probabilities as follows:

$$\begin{array}{l} n=\frac{{\left(Z_{\alpha /2}+Z_{\beta }\right)}^{2}\times \left[p_{1}\left(1-p_{1}\right)+p_{2}\left(1-p_{2}\right)\right]}{{\left(p_{1}-p_{2}\right)}^{2}}\\ \approx 72\;\mathrm{patients}\;\mathrm{per}\;\mathrm{group} \end{array}$$

Using a sample size greater than the largest estimated requirement (n ≈ 72 per group) among major outcomes will ensure sufficient power for evaluating the impact of REBOA in minimizing blood loss during cesarean sections in patients with placenta accreta spectrum disorders, adequately accounting for the detection of previously reported effect sizes with a significance level (*α*) of 0.05 and a statistical power (1−*β*) of 80%. Thus, the calculated sample size was 72 patients per group (overall 144 patients).

